### Exclusion criteria

Obvious destruction of the apical tissue or presence of large cysts or bothSevere periodontitisOral malignant tumor(s)Undergoing radiotherapyPregnancyMental illness or systemic diseasesIncapable of self-careUnsuitable for the trial as deemed by the researchers

### Dropout criteria

Poor clinical complianceVoluntary withdrawal from the trial by the patient

According to the software nQuery Advisor + nTerim 3.0, a sample size of 160 patients (80 for each group) should be recruited [30]. To allow for 20% attrition, the recruitment sample size for this trial will be 200 patients (100 in each group).

Upon fulfilment of the selection criteria, 200 eligible participants will be randomly divided into intervention and control groups in a 1:1 allocation ratio. Randomization will be performed in accordance with a random list of numbers generated by the Department of Biomedical Statistics of Southern Medical University. Five dentists will participate in this study and all of them will have received standardized training in endocrown restoration before the study begins. The number of cases assigned to each dentist is unknown and will vary because of factors outside the control of the study. These five dentists will not be involved in observations or data collection during the clinical evaluations.

### The intervention group

The intervention group will receive 90-degree shoulder endocrown restoration. The restoration will be completed by the following steps: (1) All decayed or damaged areas of the tooth will be removed, and occlusal anatomical reduction of 2.0 mm will be performed to form a 90-degree rounded shoulder margin. Gutta-percha will be removed to a depth not exceeding 2 mm and sealed with composite resin. The undercuts of the tooth cavity will be blocked out with a nano-hybrid composite resin, which will serve as a base material. A 2- to 5-degree divergence of the vertical walls will be prepared with a conical flat-end diamond bur. (2) A chair-side CEREC CAD/CAM system will be used to mill VITA SUPRINITY blocks to obtain the prosthesis. (3) Cementation, occlusion adjustment, and polishing will be performed. (4) Patients whose affected tooth receives a class A assessment according to the modified USPHS criteria of marginal adaptation will be included in this trial.

### The control group

The control group will be treated with flat endocrown restoration. In the first step of the restoration, all of the decayed or damaged areas of the tooth will be removed, and occlusal flat reduction of 1.5–2.0 mm will be achieved. The subsequent steps will be the same as those for the intervention group.

### Outcome measures

Clinical evaluations will be performed at baseline and at 24 months after treatment according to modified USPHS criteria by two independent evaluators (Table 1) [31–34]. The evaluators will complete a standardized training program before the experiment begins. If two evaluators present inconsistent evaluations during the study, a third evaluator will perform an evaluation, and the concurring evaluations from two evaluators will be used for analysis.

**Table 1 Tab1:** Modified USPHS criteria

Category	Rating	Criteria
Marginal adaptation	A	Probe, does not catch, smooth margin interface
	B	Probe catches at single spots, slight roughness
	C	Probe catches under 50% of margin length
	D	Probe catches at/over 50% of margin length
Marginal discoloration	A	No discoloration on the margin
	B	Superficial discoloration on the margin, no penetrate in pulp direction
	C	Discoloration has penetrated the margin in pulp direction
Integrity of restoration	A	Completely intact
	B	Crack apparent on transillumination
	C	Fracture observable
	D	Crown lost(state at which interface debond occurred)

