**Methods:**

The proposed flat and 90-degree shoulder marginal endocrown assessment trial is an open-label, parallel-group, multicenter randomized controlled trial involving two hospitals. A total of 200 patients will be included in this trial, and the following patient inclusion criteria will be applied: good oral hygiene habits, no periodontal diseases, receipt of standard root canal treatment, and need for endocrown restoration. Patients will be enrolled after providing signed informed consent and will be divided into two groups (flat and 90-degree shoulder endocrown) in accordance with a random number table. Treatment allocation will be balanced (1:1). Endocrowns will be cemented by dual-cured luting composite. Clinical evaluations will be performed at baseline and at 24 months after treatment in accordance with modified US Public Health Service criteria by two independent evaluators. The primary outcome will be marginal fit; secondary outcome measures will include debonding, marginal discoloration, and integrity of restoration. All acquired data will be analyzed by an independent statistician. Wilcoxon one-sample tests will be used for intra-group comparisons, and Wilcoxon two-sample tests will be used for inter-group comparisons. The Bonferroni method will be used to correct for multiple comparisons, and hierarchical logistic regression will be applied to determine central effects.

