## Methods and design

### Hypothesis

For this study, we hypothesize that the restorative effect of the 90-degree shoulder endocrown will be superior to that of the flat endocrown restoration.

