### Methods

This is a multicenter, randomized, open-label superiority trial with two balanced parallel arms. The participants will be recruited from the Departments of Conservative and Endodontic Dentistry in Nanfang Hospital of Southern Medical University and the Guanghua School of Stomatology of Sun Yat-sen University. The schedule of enrollment, interventions and assessments is showed in Fig 2.

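### The primary outcome is a probe rating in an open-label trial, and none of the three evaluators is stated to be masked to arm

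*Protocol article*

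**What the plan says.** The Methods section of the protocol article calls the study an "open-label superiority trial with two balanced parallel arms". The Hypothesis section gives a direction: "the restorative effect of the 90-degree shoulder endocrown will be superior to that of the flat endocrown restoration".

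The abstract names the endpoint: "The primary outcome will be marginal fit; secondary outcome measures will include debonding, marginal discoloration, and integrity of restoration". I read marginal fit as the marginal adaptation category of Table 1, which runs from A to D. Class A is a margin on which the probe does not catch. Class B is "Probe catches at single spots, slight roughness".

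The Outcome measures section says who rates: "Clinical evaluations will be performed at baseline and at 24 months after treatment according to modified USPHS criteria by two independent evaluators". It adds "The evaluators will complete a standardized training program before the experiment begins", and it brings in a third evaluator when the two disagree, with the two matching ratings used for analysis. The text on sample size and randomisation, printed under the Dropout criteria heading, says of the treating dentists: "These five dentists will not be involved in observations or data collection during the clinical evaluations".

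The available text nowhere says that any of the three evaluators is masked to arm, or that the third is kept unaware of the first two ratings.

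**The concern.** Marginal adaptation depends on what the examiner feels through a hand-held probe. The step from A to B is a small one: no catch against a catch at isolated points with slight roughness. Every included tooth must start at class A (Inclusion criteria, and step 4 under The intervention group), so deterioration first registers at that step.

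An evaluator who knows the arm may, without intending it, resolve borderline findings according to expectation. If evaluators share the expectation written in the Hypothesis section, doubtful flat margins would tend to be graded B more often than doubtful shoulder margins. A difference could then appear in the primary comparison with no true difference between the two forms.

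The stated safeguards address other problems. Separating operators from raters removes the operators' interest in their own work. Training and adjudication reduce random disagreement. None of them hides the arm from the person holding the probe. Two raters with the same expectation agree with each other, so the third is never called.

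**Working it through.** **Inputs from the article.** Target of 160 patients, 80 per arm; 20% attrition; two-sided 5% level; two-sample Wilcoxon test between groups; two concurring ratings decide the final grade. The recruitment figure reproduces: 160 / (1 − 0.20) = 200. It is not in dispute. I use 80 per arm as the number rated at 24 months.

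**Assumptions, not in the article.** There is no true difference between arms; a given share of teeth is truly class A; raters downgrade a share *b* of true class A flat teeth to B and make no such error in the shoulder arm.

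**Bias fully shared (all raters err on the same teeth), 80% class A, *b* = 10%.**
- Spurious gap: 0.80 × 0.10 = 0.08, so apparent class A rates are 80% and 72%, about 6 teeth (0.08 × 80 = 6.4).
- Mean rate 0.76; SE = √(0.76 × 0.24 × 2/80) = 0.0675.
- z = 0.08 / 0.0675 = 1.185.
- Chance of p < 0.05: Φ(−1.96 + 1.185) + Φ(−1.96 − 1.185) ≈ 0.22.

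This treats the outcome as A versus not A. Simulating the planned Wilcoxon test with tie correction (40,000 trials; grades A to D at 80%, 14%, 4%, 2%) gives 0.20.

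**Rater errors independent, two-of-three rule, same 80% and 10%.**
- Final grade downgraded: 3(0.1)² − 2(0.1)³ = 0.028.
- Spurious gap: 0.80 × 0.028 = 0.0224.
- Mean rate 0.7888; SE = √(0.7888 × 0.2112 × 2/80) = 0.0645.
- z = 0.0224 / 0.0645 = 0.347.
- Chance of p < 0.05: Φ(−1.613) + Φ(−2.307) ≈ 0.064.

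The same calculation gives 5.8% at 70% class A and 8.0% at 90%.

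**Sensitivity of the shared-bias case (simulated Wilcoxon test, 80 per arm).**

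| True class A | *b* = 0 | *b* = 5% | *b* = 10% | *b* = 20% |
|---|---|---|---|---|
| 90% | 0.048 | 0.13 | 0.35 | 0.82 |
| 80% | 0.050 | 0.09 | 0.20 | 0.56 |
| 70% | 0.048 | 0.07 | 0.13 | 0.37 |

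Grades B, C and D were set at 7%, 2%, 1% in the first row and 20%, 7%, 3% in the last. With no rater bias, the test holds its 5% level in all three.

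**The case against.** The strongest reply is that silence is not evidence of unmasked raters. Open-label describes the trial as a whole, and a condensed article may leave visit procedures to the full protocol or to the SPIRIT checklist and figure, which are not shown. A reader might infer that the evaluators will know the arm; the text does not say so, and the exact reading is that masking is not stated. That limit stands. The silence still matters, because who is masked is a basic design feature. The article gives the evaluators' number, training and disagreement rule and labels the trial open-label, with no exception for evaluation.

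The second reply is that the safeguards are real: written grade anchors, training, two raters, a third on disagreement, and an independent statistician. This stands in part. If rater errors are independent, the two-of-three rule cuts a 10% downgrade to 2.8% and nearly removes the inflation. It does nothing against a bias the raters share, and the statistician works on ratings already made.

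The third reply is that a reader might infer that the bias must favour the shoulder form. That is unsupported. The hypothesis belongs to the investigators, nothing shows that the evaluators hold it, and the Background says the difference between the forms is hard to predict. Bias either way, or none, is compatible with the text.

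The fourth reply is that masking may fail because the arms differ in the shape of the very margin being probed. This is a fair limit on what the fix can achieve, but it does not justify leaving masking unspecified.

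**Conclusion.** The point holds in this form: the plan describes an open-label trial with an examiner-rated primary outcome and does not state that its evaluators are masked, so the primary comparison is left open to detection bias.

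On the assumed figures (both arms truly 80% class A, 80 per arm, 10% of true class A flat teeth downgraded), the false-positive rate lies between about 6% with independent errors and about 20 to 22% with fully shared bias, against 5% with none. The article supplies neither the class A rate nor the amount or correlation of rater bias. The range is therefore an illustration, and its upper end should not be read as the expected error rate of this trial.

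**What to change.** Describe the trial as open-label for treatment with masked outcome evaluation. State that all three evaluators work without access to allocation, chart, radiograph or CAD file, and that the third does not see the first two ratings. Apply this to every rating still to be made, including the class A entry rating where evaluators make it; ratings already recorded cannot be masked afterwards. Acknowledge that masking may be partial because the margin form may be visible or felt. Asking evaluators to record a guess of the arm is optional; it would let the report show how far masking held.

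This is a cheap improvement: protocol wording and a paperwork rule at visits, with the same evaluators and no change to sample size, treatment or visit schedule. The downside is small: the extra rule and possibly incomplete masking, so a full return to the 5% level cannot be promised.

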### Data collection

The investigators will use a case report form (CRF) to collect data for the outcome analysis. The CRF includes demographic data, oral habits, medical history, and adverse events. To protect the privacy of patients, the patients will be registered with the first letters of their full name on the form. A clinical researcher will visit each center to inspect the acquired data and assess data quality by comparing the data with the medical records. The data will be entered twice into a database by designated operators and inspected by a data manager.

### Statistical methods

#### Basic principles

The data will be analyzed by an independent statistician. All statistical tests will be two-tailed. A *P* value of less than 0.05 will be the level of significance, and 95% confidence intervals will be calculated. Parametric methods will be considered first. Data that do not meet or cannot be transformed to meet parametric assumptions will be analyzed by non-parametric methods.

#### Primary outcome analysis

Wilcoxon one-sample tests will be used for intra-group comparisons, and Wilcoxon two-sample tests will be used for inter-group comparisons. The Bonferroni method will be used for multiple comparisons, and hierarchical logistic regression will be used to detect central effects.

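### With only two hospitals, a hierarchical model for centre tells little if centre is a random level, and the primary Wilcoxon test gives up power by leaving out centre and dentist

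*Protocol article*

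**What the plan says.** - **Setting.** The abstract describes a "multicenter randomized controlled trial involving two hospitals".
- **Operators.** The text on sample size and randomisation, printed under the heading Dropout criteria, says that "Five dentists will participate in this study". It adds: "The number of cases assigned to each dentist is unknown and will vary because of factors outside the control of the study". All five are to have standardised training.
- **Allocation.** The same text says that patients are "randomly divided into intervention and control groups in a 1:1 allocation ratio". The article does not say whether the list is stratified.
- **Outcome.** The abstract states that "The primary outcome will be marginal fit". Table 1 grades marginal adaptation in four ordered classes, A to D.
- **Analysis.** Under Primary outcome analysis, "Wilcoxon two-sample tests will be used for inter-group comparisons", and "hierarchical logistic regression will be used to detect central effects". No centre or dentist stratum is attached to the Wilcoxon test, and no named analysis contains a dentist term. The article does not say whether centre is a random or a fixed term.

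**The concern.** There are two separate issues, and both concern methods that the article names.

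First, a hierarchical model for centre is usually understood to treat centres as a sample from a population and to estimate the variance between them. Two hospitals give a single contrast from which to estimate that variance. A model chosen to find centre differences may then report none when they are real, and a reader could take that as reassurance.

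Second, the protocol recognises five operators with uneven caseloads, but the main comparison of the margin forms does not use that information. If results differ between dentists, those differences stay in the comparison as noise. What is at stake is the chance of detecting a true difference between arms with 80 evaluable patients per arm.

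**Working it through.** **Inputs from the article:** 2 centres, 5 dentists with unequal and unfixed caseloads, 160 evaluable patients (80 per arm), two-sided 5% tests, a four-grade ordered outcome. The article's recruitment figure reproduces: 160 / (1 − 0.20) = 200. The assumptions behind the 160 are not given in the article, and nothing below depends on them.

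**1. Precision of a centre variance.** With k units, the normal-theory 95% limits for a between-unit SD are the estimate times √(df/χ²₀.₉₇₅) and √(df/χ²₀.₀₂₅), with df = k − 1.

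| Units | df | Lower multiple | Upper multiple |
|---|---|---|---|
| 2 centres | 1 | √(1/5.024) = 0.45 | √(1/0.000982) = 31.9 |
| 5 dentists | 4 | √(4/11.14) = 0.60 | √(4/0.484) = 2.9 |

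These limits ignore sampling error within centres, so they are favourable to the model.

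**2. What a random-centre fit would return.** Random-intercept logistic models were fitted by maximum likelihood to simulated data (assumed: 160 patients, 20% event rate, equal clusters; 200 runs per setting).

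| True SD (logit) | Clusters | Fitted SD below 0.05 | 5th to 95th percentile of fitted SD |
|---|---|---|---|
| 0.5 | 2 | 46% of runs | 0 to 0.74 |
| 1.0 | 2 | 36% of runs | 0 to 2.33 |
| 1.0 | 5 | 9% of runs | 0 to 1.63 |

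With two centres and a true SD of 1.0, the median fitted SD was 0.33. A fixed centre effect needs one parameter, estimated from 160 / 2 = 80 patients per centre if the split is equal (assumed), so it is estimable.

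**3. Validity of the unstratified Wilcoxon.** Trials were simulated with 80 per arm, a four-grade outcome and five dentists of unequal caseload independent of arm (2,000 runs per setting). Type I error was 0.058, 0.058 and 0.056 at dentist SDs of 0, 0.5 and 1.0 on the logit scale. Dentist variation does not inflate it. Power at an assumed log-odds effect of 1.0 fell from 0.74 to 0.72 and 0.67 over the same SDs.

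**4. What stratifying by dentist gains.** The van Elteren test sums the within-dentist rank statistics with weight 1/(n_k + 1), where n_k is the number of patients of dentist k. Assumed: 160 patients, log odds ratio 1.0 (odds ratio about 2.7), caseload shares 30/25/20/15/10%; 2,500 runs.

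| Dentist SD (logit) | Unstratified power | Stratified power | Difference |
|---|---|---|---|
| 0.5 | 0.680 | 0.670 | −1 point |
| 1.0 | 0.642 | 0.683 | +4 points |
| 1.5 | 0.579 | 0.671 | +9 points |

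A separate simulation gave gains of about 5 points at SD 1.0 and 12 points at SD 1.5, with a cost of at most about 1 point when dentists do not differ. Hence the ranges of 4 to 5 and 9 to 12 points.

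**The case against.** The strongest reply is that the article does not fix centre as random. A fixed centre term or a centre-by-arm term can be estimated from two hospitals, dentist could be a level, and the choice of terms or of a cut-point on the four grades may stand in a SAP that is not shown. This stands: the criticism of the centre model holds only on the usual reading of a hierarchical model, and it concerns an ancillary check rather than the treatment test. It does not remove the point, because the named method suggests a random level and one sentence would settle it.

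A second reply is that the power figures rest on assumed inputs, and that standardised training may narrow differences between dentists. This also stands. It limits the size of the gain, but stratifying costs little if dentists turn out alike.

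Several stronger readings are tempting, and the documents do not support them.

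- **The centre model will fail to converge.** The simulated fits returned estimates. They were often near zero or very imprecise, which is a different fault.
- **Operator skill is confounded with margin form.** Patients are randomised individually. With 100 per arm fixed and 40 per dentist assumed, the chance that at least one dentist has a 26:14 split or worse is about 21% (25:15 or worse: about 41%). That is chance imbalance, which the test's error rate already covers. Type I error rose to 0.10 and 0.18 (dentist SD 0.5 and 1.0) only when opposite caseload patterns in the two arms were imposed, and the article describes nothing of the kind. The rule that only teeth rated class A after restoration are included could in principle disturb the balance, but nothing in the article shows that it does so by dentist.
- **The result will carry no interval.** Basic principles promises 95% confidence intervals. Which estimate they accompany can be left to the SAP.
- **The randomisation list is unstratified.** The article is silent on this, and silence in a condensed article is not an error.

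**Conclusion.** The point holds as one of efficiency and model choice, not of validity. If centre is a random level, two hospitals make its variance practically uninformative (SD limits 0.45 to 31.9 times the estimate), and the model would often miss a real centre difference. If centre is fixed, this criticism falls away and only the wording needs changing.

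The unstratified Wilcoxon remains a valid test with type I error near 5%. It forgoes about 4 to 5 points of power at a dentist SD of 1.0 and 9 to 12 points at 1.5, and nothing worth recovering at 0.5 or below. These figures assume 160 evaluable patients, a log odds ratio of 1.0, unequal caseloads independent of arm, and assumed rating distributions. The article gives neither the true variation between dentists nor the effect size, so the gain could lie anywhere in this range.

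**What to change.** 1. State that centre is a fixed effect, and examine arm-by-centre as a fixed interaction.
2. Run the primary between-arm test as a van Elteren (stratified Wilcoxon) test by dentist, or by centre if dentist strata are too small. Set the rule for that choice before outcomes are seen.
3. Report the common odds ratio with its 95% confidence interval from a proportional-odds model of the 24-month rating, with arm and dentist (or centre) as fixed factors. If each dentist works at one hospital, the dentist terms already carry centre.

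The cost is a change of analysis wording, a few degrees of freedom (four for five dentists, one for two centres), and up to about 1 point of power if dentists hardly differ. The one data requirement is that the treating dentist is on record for each patient. The article reports that recruitment was still under way, so at that stage the change could be made before the 24-month results were known.

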#### Secondary outcome analysis

For intra-group comparisons, paired *t* tests or Wilcoxon one-sample tests will be used for quantitative variables, and McNemar tests will be used for qualitative variables. For inter-group comparisons, quantitative variables will be analyzed by one-way analysis of variance (more than two groups) and two-sample *t* tests (two groups) or by non-parametric methods. Qualitative variables will be analyzed by Pearson’s chi-squared tests. Non-parametric data will be analyzed by the Kruskal–Wallis test.

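### Marginal discoloration and integrity are ordered ratings, but the secondary analysis, read plainly, gives them an order-blind chi-squared test between arms and a two-level McNemar test within arms

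*Protocol article*

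**What the plan says.** The abstract of the Protocol article lists the outcomes: "secondary outcome measures will include debonding, marginal discoloration, and integrity of restoration". Table 1, under Outcome measures, defines the scales. Discoloration has three levels, the worst being "Discoloration has penetrated the margin in pulp direction". Integrity has four, the worst being "Crown lost(state at which interface debond occurred". Debonding itself is a yes/no event.

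Secondary outcome analysis assigns tests by type of variable and does not say which type each outcome is:
- Within groups, "McNemar tests will be used for qualitative variables"; paired t tests or Wilcoxon one-sample tests are for quantitative variables.
- Between groups, "Qualitative variables will be analyzed by Pearson’s chi-squared tests".
- Between groups, t tests, analysis of variance or non-parametric methods are for quantitative variables.
- A last sentence gives the Kruskal–Wallis test to data described as non-parametric.

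Basic principles adds: "Parametric methods will be considered first", with a non-parametric fallback. Primary outcome analysis uses Wilcoxon one-sample and two-sample tests for marginal adaptation, an A to D rating from the same Table 1.

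**The concern.** Two of the three named secondary outcomes are ordered ratings of the same kind as the primary outcome, but by the natural reading they are tested differently and no reason is given.

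Between arms, Pearson's test treats A, B, C and D as unordered labels. It spreads its sensitivity over every way the two distributions can differ, while the trial's hypothesis is directional in kind: one margin form wears better than the other. A rank test concentrates on that shift. At stake is the chance of seeing a real difference in discoloration or integrity.

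Within arms, the standard McNemar test needs a paired two-by-two table. A 3-level or 4-level rating does not form one unless it is dichotomised, and no cut is stated.

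**Working it through.** **Sample size.** The article gives 160 evaluable patients, 20% attrition and 200 recruited. 160 / (1 − 0.20) = 200, which reproduces. The comparison below uses the 80 evaluable patients per arm and a two-sided 0.05 level, both from the article. The article gives no rating distributions, so every distribution below is an assumption.

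**Hand check, discoloration.** Assume A/B/C of 60/25/15% in one arm and 78/16/6% in the other.
- Counts: 48/20/12 against 62.4/12.8/4.8. Expected counts per arm: 55.2, 16.4 and 8.4.
- Pearson: 2 × (7.2²/55.2 + 3.6²/16.4 + 3.6²/8.4) = 1.88 + 1.58 + 3.09 = 6.54 on 2 degrees of freedom.
- Wilcoxon: the mid-ranks are 55.7, 127.3 and 152.1, so W = 48 × 55.7 + 20 × 127.3 + 12 × 152.1 = 7044.8. Its null mean is 80 × 161 / 2 = 6440. The tie-corrected variance is (80 × 80 / 12) × (161 − 54.46) ≈ 56,822. So z = 604.8 / √56,822 = 2.54 and z² = 6.44 on 1 degree of freedom.

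The two statistics carry almost the same signal (6.54 and 6.44). Pearson has to exceed 5.99 (2 degrees of freedom), Wilcoxon only 3.84 (1 degree of freedom). With four levels Pearson's threshold rises to 7.81. That is where the power goes.

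**Simulation, specified distributions** (80 per arm; uncorrected Pearson with empty columns dropped; tie-corrected Wilcoxon):

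| Scenario | Wilcoxon | Pearson |
|---|---|---|
| Discoloration 60/25/15 vs 78/16/6, power | 73% | 63% |
| Integrity 86/5/5/4 vs 97/1/1/1, power | 74% | 49% |
| No difference, 94/2/2/2 in both arms, size | 4.8% | 2.0% |

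**Simulation, proportional-odds shifts** (6,000 runs each; power at odds ratio 2 / 2.5 / 3):

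| Control-arm distribution | Pearson | Wilcoxon |
|---|---|---|
| 60/30/10 | 43 / 66 / 79% | 54 / 76 / 87% |
| 85/12/3 | 20 / 29 / 39% | 27 / 40 / 51% |
| 50/25/15/10 | 44 / 68 / 82% | 62 / 82 / 93% |
| 88/5/4/3 | 11 / 16 / 22% | 24 / 33 / 43% |

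The smallest loss is about 7 points (85/12/3, odds ratio 2). The largest is 25 points (integrity in the first table, 74 − 49).

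**Error rate.** With no difference between arms, Pearson's size was 3.9 to 4.9% in the second set and 2.0% for 94/2/2/2. Wilcoxon stayed at 4.6 to 5.3%. In the two rare-rating rows (85/12/3 and 88/5/4/3), 96 to 100% of simulated tables had an expected count below 5.

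**Debonding.** As a binary outcome (assumed 10% vs 2%), Pearson and Wilcoxon have the same power, 58%. The loss concerns only the ordered ratings.

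**The case against.** The strongest reply is that the section already names an order-respecting test. With two groups the Kruskal–Wallis test is equivalent to the Wilcoxon two-sample test, and Basic principles has a non-parametric fallback. Mapping each outcome to one test can also properly be left to an SAP that is not shown. This stands in part: nothing new has to be invented, and the lack of a full mapping is not the point here. But the article does state a rule for qualitative variables, and a letter rating falls under it more naturally than under a sentence about non-parametric data.

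A reader might infer more than the documents support:
- *That Pearson's test is invalid or inflates false positives.* Its size is at or below 5% throughout. It is inefficient and, when sparse, conservative.
- *That sparse cells spoil both outcomes.* In the discoloration example the smallest expected count is 8.4. Sparsity depends on how rare poor ratings turn out to be and is likelier for integrity. The 92.5% and 94–100% success rates in Background are not rates of an A rating, because B for integrity is only a crack on transillumination.
- *That t tests and ANOVA are applied to the ratings.* The text limits them: "quantitative variables will be analyzed by one-way analysis of variance (more than two groups) and two-sample" t tests. No named secondary outcome is quantitative and there are two arms, so these lines are never triggered.
- *That McNemar fails because every crown starts at A.* Class A at entry is required only for marginal adaptation. For the other ratings it is an inference, and an empty discordant cell would not invalidate the test. The objection is the number of levels.
- *That chi-squared and McNemar are wrong for all secondary outcomes.* Both suit binary debonding in kind, sparse cells aside.

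**Conclusion.** The point holds in limited form. Read plainly, Secondary outcome analysis sends two ordered ratings to a between-arm test that ignores their order and to a within-arm test that does not fit them as written, out of line with the primary analysis. The between-arm cost is about 7 to 25 percentage points of power at 80 per arm, with conservative size (about 2 to 4%) when poor ratings are rare. The direction is the same in every scenario tried; the size rests on assumed distributions and on differences that shift the ratings one way. No false-positive risk has been shown, the primary outcome is untouched, and binary debonding is not affected. The change is worth making because the gain is real and the cost is close to nil.

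**What to change.** In Secondary outcome analysis, or in the SAP if one governs, state that:
- Discoloration and integrity at 24 months are compared between groups with the Wilcoxon two-sample test, which is the Kruskal–Wallis test already named when there are two groups. Use an exact or permutation version if the table is sparse.
- Within groups, these two ratings are compared with the Wilcoxon one-sample test, as for the primary outcome.
- Debonding, as a yes/no outcome, keeps a two-by-two test, with Fisher's exact test if expected counts are small, and is reported as a risk difference with a confidence interval.

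Removing the t-test and ANOVA lines, which match no named outcome, is optional tidying. The cost is analysis wording only: no change to sample size, visits or data collected. It should be fixed before 24-month data are examined.
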